## Abstract

**Background:**

Within professional European competitions, matches can be played in extreme environmental temperatures, ranging from −5 °C to +30 °C in different countries. Furthermore, the World Cups are usually played in the summer months, when temperatures can exceed 35 °C, increasing physiological stress. Practical and cost-effective cooling strategies may be implemented to help players and referees to cope with exercising in the heat. No study has evaluated the effect of non-thermal internal cooling techniques regarding performance responses on elite football referees, so far. This study aims to analyse the effects of a menthol mouth rinse regarding physical, physiological, and perceptual performance in elite male football referees, during a 90-min football protocol in the heat.

**Methods:**

At least thirteen male football referees will be recruited to perform two intermittent football protocols, separated by no less than 7 days. After passing the eligibility criteria, the participants will be randomly assigned to 1 of 2 beverages: (1) intervention - menthol solution 0.01% and (2) placebo - noncaloric berry-flavored solution, both at room temperature. The beverages will be given before warm-up (pre-cooling) and at the half-time (per-cooling). The trials will follow a randomized counterbalanced crossover design, single blinded, and will take place in indoor facilities, with Wet Bulb Globe Temperature (WBGT) > 30 °C, at the same time of the day to control for circadian variations.

**Impact of the project:**

The results of this study are expected to determine whether mouth rinsing a menthol solution before and during a football exercise protocol performed in the heat will alter perceptual measures and help ease physiological strain and attenuate performance decrements in elite male football referees, comparing to a non-cooling strategy. Thus, we can be closer to defining nutritional strategies of internal cooling that may be an advantage for the performance of the football referees in the heat.

**Trial registration:**

www.ClinicalTrials.gov NCT05632692 registered on 20 November 2022.

## Introduction

1

Sports competitions take place in a great diversity of geographical areas, some characterized by hot environments, being anticipated that an increasing number of competitions are and will be held in adverse ambient conditions due to climate change, which is expected to aggravate over the coming years [1]. For instance in Europe, football matches have been reported to be played in extreme environmental temperatures ranging from −5 °C in Norway, to +30 °C in Spain [2]. Moreover, to facilitate the congested European league season, the FIFA World Cup and the UEFA European Championship are usually played during the summer, when temperatures can exceed 35 °C, with potentially high levels of humidity [3,4].

Thermal challenges in sports events carried out under heat stress might influence athletic and cognitive performance, through an increase in core temperature (Tcore) and individual sweating rate (SR) responses, especially for those who live and perform in more temperate climates [5]. As a consequence of the rise of the SR, the risk of dehydration is significantly increased [6]. Dehydration is detrimental to thermoregulatory function during exercise in the heat, resulting in an inhibition of reflex heat dissipation mechanisms of sweating and cutaneous vasodilation, hampering core body temperature maintenance [7,8].

Referees' physical activity during a football match induce a mean total body water loss of 1.60 ± 0.13 L (i.e, mild 2.0% dehydration) [9]. Such a level of dehydration, induced by water restriction, heat, or physical exertion (or a combination of these), cause a reduction in physical [10], psychomotor [11], and cognitive performances, even in temperate environments (22.0 °C ± 2.0 °C, 60.0%–70.0% relative humidity) [12]. In moderately high environmental temperatures (∼30 °C), sprint and jump performances decreased markedly in the last 15 min of a football match [[13], [14], [15]]. 10.13039/100014337Furthermore, a marked reduction in high-intensity running has been observed in a standardised set-up in matches played in hot environments [15], and supported by retrospective analyses of the 2014 FIFA World Cup [16].

During football competition in extreme temperatures, players can modify their game in order to maintain performance and prevent fatigue [17], through the flexibility to adjust game intensity, especially when they are “off-the-ball.” Referees, though, have to follow the rhythm of the match and maintain closeness to match events so that correct decisions can be made [18]. Therefore, although previous research showed that the physiological and physical demands of elite-standard football referees are similar to those of a midfield football player [19,20], these demands may increase under more extreme temperatures since they cannot use the same coping strategies [3]. Thus, heat stress may have detrimental effects on performance and sudden or extreme exposure is a major health concern in this population [15,16].

Several thermal (cooling) strategies have been tested and used with the primary goal of reducing central temperature and thermal sensation (TS), and further delaying the onset of hyperthermia-induced fatigue [21]. These can be applied externally (e.g., using a cooling vest, ice pack, cold-water immersion, topically applied menthol) or internally (e.g., ice slurry, crushed ice, cold beverage ingestion, menthol mouth rinsing) [22]. As a matter of fact, ice slurry ingestion has shown to decrease central and brain temperature, and to improve thermal perception via the stimulation of thermoreceptors located within oral and abdominal regions [22,23]. This has led to an increase in the use of this method in professional competitions performed in hot and humid environments [24].

Research on non-thermal internal cooling methods has increased recently, with particular attention to L-menthol, due to its properties in relieving thermal strain associated with exercise in the heat. Menthol oral application stimulates the mandibular and maxillary branches of the trigeminal nerve (which are predominantly responsible for the detection of temperature and nociceptive stimuli across the face and within the oral cavity) and has consistently shown to improve thermal comfort (TC) and decrease TS, which are thought to modulate perceived exertion to improve performance in the heat [24,25].

A recent systematic review found that rinsing a menthol solution (0.01%) during exercise in the heat significantly improved physical performance (by 3.6–34.4%), mainly in continuous exercises. Conversely, less favourable results were reported for thermal techniques, with less than half of the studies revealing significant improvements in physical performance [26]. However, most of the clinical trials carried out in this area predominantly involve endurance exercise protocols with recreational athletes. It has been pointed out that it is urgent to evaluate the effect of internal cooling strategies on intermittent exercises, especially in elite sports. In this context, the studies carried out concerning internal cooling strategies did not include referees, despite a negative impact of heat stress on both physical and cognitive performance being already well established.

Therefore, the present manuscript intends to propose a protocol for a randomized crossover trial, which aims to analyse the effects of a menthol solution mouth rinse, comparing to a non-cooling strategy, on perceptual, physical and physiological performance responses, in elite male football referees, during a standardised laboratory exercise protocol performed in the heat that aims to mimic the intermittent and multi-directional nature of running in football match-play.

## Methods and analysis

2

The study has been approved by the Ethics Committee of the Faculty of Nutrition and Food Sciences of University of Porto, Portugal (Report 112/22 CEFCNAUP 2022) and will be conducted in accordance to the declaration of Helsinki for human studies [27]. The study protocol was developed considering the guidelines from Consolidated Standards of Reporting Trials (CONSORT) [28] and the Recommendations for Interventional Trials (SPIRIT) [29].

### Sample size and recruitment

2.1

For sample size and statistical power calculations, power analysis was based on changes in TS after the internal administration via mouth-rinsing or ingestion of menthol solution. Considering a type I error of 5% and a power of 90%, with a statistical significance (p-value ≤0.05) and a moderate effect size of 0.54 (differences in TS were considered following Jeffries and Waldron results [30]), a total of 10 participants will be needed (using G*Power 3.1.9.2 ®). Considering a drop-out rate of 30% throughout the study, 13 participants as a buffer against attrition.

The Portuguese Football Federation (PFF) will contribute by recruiting referees through direct contact, databases, and referral sources. Following an initial telephone screen to determine the eligibility of potential participants, an orientation session (introductory meeting) will be scheduled to offer detailed information about the study, including the number and type of assessments, the length and nature of the exercise training, and the time commitment required to complete the study. After eligibility criteria confirmation, all participants will sign an informed consent form before being allocated to the study. Participants’ privacy and confidentiality will be guaranteed during and after investigation according to the Portuguese data protection law. Privacy, anonymity, and confidentiality of data/information identifying the participants will be strictly maintained. All information and results of the tests performed on the participants will be confidential. No one other than the investigators of this research will have access to the data.

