### Study design, setting and randomization

2.3

A randomized counterbalanced crossover trial with two conditions will be carried out. After passing the eligibility criteria and attending the introductory meeting and a familiarization visit, the participants will be assigned to 2 experimental days for undergoing 2 different randomly ordered experimental conditions. Each condition will be comprised of a 90-min football protocol (SAFT 90) [31], with the administration of one of 2 beverages before warm-up (5 min of pre-cooling) and at the half-time (5 min of per-cooling). There will be a minimum washout period of 7 days between each trial, to reduce carryover effects from the previous condition and to assure an adequate exercise recovery. The trials will take place in an indoor environment, with Wet Bulb Globe Temperature (WBGT) values exceeding 30 °C, at the same time of the day, to control for circadian variations.

After the familiarization visit, the allocation sequence for the order of the experimental conditions will be assigned through individual randomization from a computer-generated random order, equally assigned to every participant, by the main researcher. Randomization will be concealed through a password-protected document that will not be revealed until the first trial. The main researcher will not be blinded in this type of study condition and will have access to the allocation sequence list and will retrieve the randomization code prior to each experimental to prepare the beverages. All the other investigators and the outcomes assessors will be blinded to study condition and group allocation, as well as participants will be blind to the beverages content and aim of the study.

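### Section 2.1: 10 participants, 90% power and a moderate effect of 0.54 do not fit together for the menthol–placebo contrast on the natural reading, and the scale, test, sidedness and correlation needed to check them are not given

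*Protocol article*

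**What the plan says.** The protocol article, section 2.1 (Sample size and recruitment), says that the "power analysis was based on changes in TS" (thermal sensation) after menthol is given by mouth. The inputs are "Considering a type I error of 5% and a power of 90" per cent, a significance threshold of p ≤ 0.05, and "a moderate effect size of 0.54" taken from a cited earlier study. The result is "a total of 10 participants will be needed (using G*Power 3.1.9.2"). This is then raised to 13 for drop-out.

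Section 2.3 fixes the design: "A randomized counterbalanced crossover trial with two conditions will be carried out". Section 2.7 plans one-way repeated-measures ANOVA for the effect of the intervention, and a two-way repeated-measures ANOVA across time in both conditions.

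Section 2.1 does not say whether 0.54 is a paired standardised difference, a difference on the raw SD or Cohen's f. Nor does it name the test family, the sidedness, the number of measurements or the correlation between conditions.

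**The concern.** Each referee receives both beverages, so the contrast of interest is a within-person difference between two conditions. For two conditions, one-way repeated-measures ANOVA is equivalent to a paired t-test. A standardised difference of 0.54 is conventionally moderate, and ten pairs are far too few to detect a paired difference of that size with 90% power.

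This paragraph is the only justification given for the size of the trial. If 0.54 is a paired difference, a reader is told that a true effect of that size would be missed one time in ten, when it would be missed about two times in three. A null result on thermal sensation could then be taken as evidence of no effect. If 0.54 is Cohen's f, the power may be close to what is claimed, but for an effect about twice the size that the wording suggests.

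**Working it through.** **Inputs from the article.** Alpha 0.05, power 0.90, effect 0.54 (called moderate), N = 10 (section 2.1); two conditions within each participant (section 2.3). Scale, sidedness and correlation ρ are not stated, so each is varied as an assumption.

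**Step 1. Can the stated 10 be reproduced?** Not from the stated inputs alone, so each plausible scale is tried in turn.

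**Step 2. 0.54 as a paired standardised difference (dz).** Power is the tail probability of a noncentral t with n − 1 degrees of freedom and noncentrality dz × √n. For n = 10 the noncentrality is 0.54 × √10 = 1.71.

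| Completers | Power, two-sided | Power, one-sided |
|---|---|---|
| 9 | 29.8% | – |
| 10 | 33.3% | 47.3% |
| 13 | 43.3% | 57.6% |

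The smallest n for 90% power is 39 two-sided and 31 one-sided. As a rough check, the two-sided normal approximation is ((1.960 + 1.282)/0.54)² ≈ 36.0, rounded up to 37. The stated 10 is not reproduced.

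**Step 3. What 10 completers can detect.** Two-sided 90% power at n = 10 needs dz of about 1.16 (1.155 on a grid of 0.001). That is 1.155/0.54 = 2.1 times the stated figure.

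**Step 4. 0.54 as d on the raw SD.** Here dz = d/√(2(1 − ρ)).

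| ρ | dz | Two-sided power at n = 10 | n for 90% |
|---|---|---|---|
| 0 | 0.38 | 19% | 75 |
| 0.5 | 0.54 | 33% | 39 |
| 0.7 | 0.70 | 50% | 24 |
| 0.8 | 0.85 | 67% | 17 |
| 0.9 | 1.21 | 92% | 10 |

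Setting dz = 1.155 gives ρ = 1 − (0.54/1.155)²/2 = 0.89. One-sided, the correlation needed is about 0.86.

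**Step 5. 0.54 as Cohen's f, repeated-measures ANOVA, two measurements.** In the G*Power form, λ = N × m × f²/(1 − ρ), with m = 2.

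- ρ = 0.5: λ = 10 × 2 × 0.2916/0.5 = 11.66; power at n = 10 is 85.9%, and 90% needs N = 12.
- ρ = 0.6: λ = 5.832/0.4 = 14.58; power at n = 10 is 92.3%, and 90% needs N = 10.

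So 10 can be reproduced on this scale. With two conditions, however, d = 2f = 1.08, and dz = 1.08/√(2(1 − ρ)) is 1.08 at ρ = 0.5 and 1.21 at ρ = 0.6. That is a large effect.

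**Step 6. Settings with more measurements.** Table 1 schedules thermal sensation at 14 points per session, so such settings have to be considered. Two that give N = 10 are:

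- f = 0.54, two groups by three measurements, ρ = 0.5: power 93.4%.
- f = 0.27 (that is, d = 0.54), 14 measurements, ρ = 0.6: power 91.2%.

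The first assumes two separate groups, whereas this trial has one group that receives both beverages. The second powers a comparison among time points. Neither is the power of the menthol–placebo contrast.

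**The case against.** The strongest reply is that the calculation is under-described rather than wrong. The article names G*Power and plans repeated-measures ANOVA, and in G*Power that family takes Cohen's f as its input. With f = 0.54 and two measurements, a correlation of 0.6 gives exactly 10, and 0.5 gives 86% power, far from 33%. A correlation of 0.6 between two sessions in the same person is not unusual. Settings with several measurements also reach 10. The word moderate is a loose label, and the study behind the 0.54 is not at hand.

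Most of this stands. A reader might infer that the trial has 33% power, or that the authors made an arithmetic error. The article supports neither, because it does not say which scale was entered. The chance of missing the effect two times in three likewise applies only if 0.54 is a paired difference.

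The reply does not clear the paragraph, though. Each route to 10 that was found needs something that the article does not state or that sits badly with it: an effect that is not moderate, a correlation near 0.89, or a term or design other than the menthol–placebo contrast. Nor is this detail that an article may leave to a fuller document. The article itself prints effect, alpha, power and N, and describes the effect.

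**Conclusion.** The point holds in conditional form. For the two-condition crossover, the printed combination of 10 participants, 90% power, alpha 5% and a moderate effect of 0.54 is not consistent on the natural reading, and cannot be verified on any other without inputs that the article omits.

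The size depends on the scale. At n = 10, two-sided power is about 33% if 0.54 is a paired difference; 19% to 92% if it is d on the raw SD, for correlations from 0 to 0.9; and 86% to 92% if it is Cohen's f with two conditions and a correlation of 0.5 to 0.6. Whatever was entered, ten completers give 90% two-sided power for the paired contrast only at a standardised difference of about 1.16 or more. These figures assume the exact t or F distribution and one summary value of thermal sensation per condition.

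**What to change.** Restate section 2.1 as follows:

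- Name the test, its sidedness, the effect-size scale and the within-participant correlation actually used, with the number of measurements if more than two.
- Give the power for the paired menthol–placebo contrast on thermal sensation: with 10 completers and a two-sided 5% test, 90% power only for a paired standardised difference of about 1.16 or more.
- If 0.54 is a paired difference, replace 90% with about 33%.
- If 0.54 is Cohen's f, say so, give the correlation, drop the word moderate and state the equivalent paired difference (1.08 at a correlation of 0.5, 1.21 at 0.6). If the correlation was 0.5, the figures also need to read 86% power at 10, or N = 12.
- If 0.54 is d on the raw SD, state the correlation and what supports it.

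The cost is the rewording of one paragraph. The correction itself requires no extra participants. The downside is a less favourable stated power or a larger stated detectable effect. The article's trial status statement says that the trial is not yet ongoing, so at this version the change can be made before recruitment.

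### The minimum of 13 referees covers 23% drop-out, not the stated 30%; for 10 completers at 30% the matching minimum is 15

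*Protocol article*

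**What the plan says.** Section 2.1 (Sample size and recruitment) of the protocol article bases the sample size on thermal sensation, with 5% type I error, 90% power and a "moderate effect size of 0.54". It concludes that "a total of 10 participants will be needed". The next sentence allows for attrition: "Considering a drop-out rate of 30% throughout the study, 13 participants as a buffer against attrition".

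The Methods part of the abstract gives the same number as a lower limit: "At least thirteen male football referees will be recruited".

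Section 2.7 (Statistics) says that missing data will not enter the analysis and that participants who discontinue or deviate will be excluded. Section 2.3 describes a two-condition crossover, so the comparison is within the person and needs both sessions.

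**The concern.** The three figures in section 2.1 (10 needed, 30% drop-out, 13 recruited) do not fit together. Thirteen is what results from adding 30% of the required number. The stated rate applies to a different base, namely those who enter. Taking 30% from 13 leaves fewer than 10.

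Attrition matters in this trial. A referee who misses one of the two sessions gives no within-person contrast, and section 2.7 describes nothing that would recover partial data. The Discussion expects some difficulty in retaining participants. It also places all recruitment in September 2023 and the end of the study by October 2023, which leaves little time to replace losses. The minimum should therefore be right before recruitment starts.

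**Working it through.** **Inputs**
- Required completers: n = 10 (section 2.1), taken as given.
- Drop-out rate: d = 0.30 (section 2.1).
- Recruitment minimum: N = 13 (section 2.1; abstract, Methods).
- Losses leave the analysis (section 2.7).

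**Step 1. Reproduce the plan's figure.** n × (1 + d) = 10 × 1.30 = 13. This matches exactly.

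**Step 2. Apply the rate to those enrolled.** The expected number of completers is N × (1 − d). Setting this to at least n gives N ≥ n/(1 − d) = 10/0.70 = 14.29, so N = 15.

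**Step 3. Expected completers at 30% loss**

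| Enrolled | Expected completers |
|---|---|
| 13 | 13 × 0.70 = 9.1 |
| 14 | 14 × 0.70 = 9.8 |
| 15 | 15 × 0.70 = 10.5 |

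Fifteen is the smallest number that keeps the expectation at or above 10.

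**Step 4. What 13 does cover.** (13 − 10)/13 = 3/13 = 23.1%.

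**Step 5. Chance of reaching 10.** The article gives no drop-out model. If losses are assumed independent, each with probability 0.30, the number of completers is binomial(N, 0.70). The probability of at least 10 is 0.42 for N = 13, 0.58 for N = 14 and 0.72 for N = 15. So 15 meets the target on average but does not guarantee it.

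**Step 6. What one completer fewer costs in power.** The article does not give the test, the type of effect size or the correlation behind the 10, so only a range under assumptions can be shown (5% level, two-sided for the paired test). For repeated-measures ANOVA the noncentrality is N·m·f²/(1 − ρ), with m − 1 and (N − 1)(m − 1) degrees of freedom. For the paired t-test it is d√N with N − 1 degrees of freedom.

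| Assumed reading of 0.54 | Power at 10 | Power at 9 |
|---|---|---|
| f, m = 4, ρ = 0.3 | 0.905 | 0.863 |
| f, m = 2, ρ = 0.5 | 0.859 | 0.809 |
| paired standardised difference | 0.333 | 0.298 |

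In these three readings the loss from 10 to 9 is about 3.5 to 5 percentage points.

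**The case against.** **Thirteen is a floor.** The abstract says at least thirteen, so the trial may enrol 15 or more. This stands, and it rules out saying that the trial will end short. It does not rescue the figure. A trial that recruits exactly 13 complies with the text and, at the text's own drop-out rate, expects 9.1 completers.

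**The 30% could mean a margin on top of 10.** On that reading 13 is right. But the sentence calls it a drop-out rate throughout the study, which is a proportion of participants in the study. If a margin of three people was meant, the wording needs changing anyway.

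**The gap is small.** It is two recruits and about one expected completer. This stands and is why the point is minor.

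**Stronger readings that the document does not support**
- A reader might infer that the stated 90% power fails because of this slip. Step 6 shows a loss of a few points in the readings tried. Whether 10 gives 90% power at all depends on assumptions the article does not state; that is a separate question, which a change from 13 to 15 would not settle.
- A reader might infer that an odd number defeats the counterbalancing. Section 2.3 assigns the order only after the familiarization visit, so 13 recruited does not fix the number randomised. The floor also permits 14. A 7:6 split is the closest possible with 13 and is trivial, and drop-out can unbalance an even start just as well.
- A reader might infer simple, unrestricted randomisation of order, with a risk of a lopsided split. The text says "individual randomization from a computer-generated random order, equally assigned to every participant" and calls the design counterbalanced. The word individual names the unit and does not exclude a restricted list. Details of how the list is restricted are commonly left to the full protocol.

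**Conclusion.** The point holds as a minor correction to a stated figure. With 10 taken as given, the plan inflates by 10 × 1.3 where 10/0.70 is needed. The stated minimum of 13 is therefore two below the 15 that matches a 30% drop-out, and it covers 23%.

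The conclusion rests on two things: reading the 30% as a share of those enrolled, and the rule in section 2.7 that takes losses out of the analysis. The independent drop-out model bears only on the probabilities in step 5, and the assumed effect-size readings only on step 6. The validity of the treatment comparison is not affected.

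**What to change.** Change the attrition sentence in section 2.1 in one of two ways:

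1. Keep 13 and say that it allows for up to 3 losses among 13 recruited, that is 23% attrition. This costs one sentence, and the abstract can stay as it is.
2. Keep 30% and state that the matching minimum is 15 (10/0.70 = 14.3, rounded up). Change the minimum in the abstract to fifteen as well. This costs two sentences and, at the minimum, two more referees.

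The choice depends on whether the investigators still expect to lose 30%. If they do, the second option is the consistent one.
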